4. MRI
5. QOL (including ADL)
6. Adverse event
7. Concomitant medications

6.2.4.3　(In case of additional treatment) 3 months after additional administration (12 weeks after additional administration) <Discontinued cases>

If administration is discontinued after additional treatment, observation and examination will be performed according to "6.2.4.1 Time of discontinuation " and "6.2.4.2 3 months after administration (12 weeks after administration) <discontinued cases> " starting from the date of additional administration.

7.　Termination of the subject's treatment or evaluation

7.1　Termination (discontinuation) of treatment of individual subjects

The investigator and subinvestigator will discontinue the administration of the investigational drug and discontinue this clinical trial for subjects who fall into any of the following categories. If an adverse event has occurred at the time of discontinuation, the investigator and subinvestigator will take appropriate measures for the adverse event and follow up the outcome of the adverse event to the extent possible, with a deadline of the end date of this entire clinical trial (scheduled last observation date for all subjects).

- The subject or surrogate withdraws consent for the administration of the investigational drug or for participation in the clinical trial (for any reason)
- If continued participation in the clinical trial is likely to endanger the subject
- When "4.1.12 Criteria for discontinuation of investigational drug " is applicable.
- If a subject is found not to meet the eligibility criteria
- If the investigator or subinvestigator determines that the subject or surrogate is unable to comply with the study protocol
- If the subject is unable to come to the hospital due to personal reasons on the subject's side (e.g., relocation, hospital transfer, etc.)
- If the subject becomes pregnant
- Other medical reasons (e.g., surgery, adverse events, other diseases, etc.) that make it impossible to administer the investigational drug
- When the investigator or subinvestigator determines that it is appropriate to discontinue the clinical trial for other reasons

7.2　Discontinuation of the clinical trial

If any of the following reasons apply, the Coordinating Committee shall, suspend the entire clinical trial or the clinical trial at a specific site. If necessary, the Efficacy and Safety Evaluation Committee will be consulted, and a decision on whether or not to continue the clinical trial (continuation, suspension, or discontinuation) will be made based on the recommendation of the Efficacy and Safety Evaluation Committee. Details of the Efficacy and Safety Evaluation Committee are separately stipulated in the "Procedures for the Efficacy and Safety Evaluation Committee.

- - Efficacy or safety information that may have a significant impact on the continuation of the clinical trial is discovered
  - When there is a violation of GCP or a violation of the study protocol that hinders the proper conduct of the clinical trial
  - Serious or continuing noncompliance by the investigator or subinvestigator is discovered
  - When it becomes impossible to continue the clinical trial due to a change in the principal investigator
  - When it is deemed impossible to reach the planned target number of cases (discontinuation of the entire clinical trial or at a specific site)
  - When the site no longer meets the requirements to properly conduct the clinical trial
  - If the IRB decides to discontinue the clinical trial
  - In the event of a recommendation from the regulatory authority to cease and desist
- When the Coordinating Committee determines that it is appropriate to discontinue the clinical trial for other reasons

8. Statistical analysis

Due to differences in disease characteristics, cystic and diffuse lesions will be analyzed separately as separate cohorts for all endpoints.

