| Efficacy endpoints | The efficacy evaluations below refer to the case of single administration. If additional treatment is given, evaluation is conducted 3 months after additional administration (1 month after additional administration for number 2 in "2.2 Other secondary endpoints" below) compared to that before the first administration.   1. Primary Endpoint   20% or more reduction in volume of venous malformations at the time of 3 months after intervention   1. Secondary endpoint   2.1 Significant secondary endpoint  Improvement in symptoms such as pain originated from venous malformations at the time of 3 months after intervention  2.2 Other secondary endpoints  1) Reduction rate in volume of venous malformations at the time of 3 months after intervention  2) Improvement in symptoms such as pain originated from venous malformations at the time of 1 months (4 weeks) after intervention  3) Improvement of QOL (ADL) at the time of 3 months after intervention   1. Other endpoints   Change in appearance at the time of 3 months after intervention; significant improvement, moderate improvement, no change and exacerbation. |
| Safety endpoints | Adverse events, side effects, laboratory values |

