4.1.6　Dosage and administration

Inject 5% ethanolamine oleate directly into the lesion at a maximum dose of 0.4 mL/kg. The same method of administration is used for children (under 15 years of age). However, the maximum dose per treatment should be 30 mL (as prepared drug solution).

[Method of calculating the maximum dose (mL)]

(1) Measure the subject's body weight (kg) (to the first decimal place). If the second decimal place can be measured, it shall be rounded off and calculated to the first decimal place.

(2) Calculate the maximum dose (mL) using the following formula based on body weight. Round off the second decimal place and calculate to the first decimal place.

Maximum dose (mL) = 0.4 (mL/kg) x body weight (kg) <up to 30 mL>

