8.1　Analysis population

8.1.1　Definition of analysis population

The population to be analyzed is defined as follows.

(1) Full analysis set (FAS): all subjects who were administered the study drug

(2) Per protocol set (PPS): The subjects in the FAS, excluding those with the following serious violations of the study protocol regulations in terms of study methods, concomitant therapy, etc. The PPS will be set for the purpose of confirming the stability of the primary analysis for the efficacy endpoints.

・Inclusion criteria violation

・Exclusion criteria violation

・Significant deviations from the study protocol that could affect the evaluation of efficacy

(3) Safety analysis set (SAS): Same as FAS

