8.1.2　Endpoints and analysis populations

The analysis population for each endpoint is shown in Table 8.1.2-1. The primary analysis population for the efficacy endpoints is the FAS.

Table 8.1.2-1 Evaluation items and analysis population

| Evaluation item | Analysis population | |
| --- | --- | --- |
|  | Cystic lesion | Diffuse lesion |
| Subject basic information | FAS | FAS |
| Primary endpoint | FAS, PPS | FAS, PPS |
| Secondary endpoints | FAS, PPS | FAS, PPS |
| Safety endpoints | SAS | SAS |

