8.2.2.4　Subgroup analysis

For "8.2.2.1 Analysis for primary endpoint" and "8.2.2.2 Analysis for secondary endpoints," a subpopulation analysis will be conducted for four age categories: 5 years and younger, 6 to 11 years, 12 to 14 years, and 15 years and older.

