8.2.3　Safety analysis

(1) For each adverse event and adverse drug reaction, the number of subjects and incidence rate are shown. The number of subjects and the incidence rate is tabulated by organ, symptoms findings, and grade of adverse event. For serious adverse events, the number of subjects and the rate of occurrence should is indicated and listed.

(2) Summary statistics of laboratory measurements are tabulated by survey period.

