8.6　Target number of cases and rationale for setting

8.6.1　Target number of cases

44 cases (22 cystic lesions, 22 diffuse lesions)

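### The protocol plans no overall safety summary, so each adverse-event rate is to be reported within a cohort of about 22 subjects

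*Protocol*

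**What the plan says.** Section 8 begins with a general rule: "Due to differences in disease characteristics, cystic and diffuse lesions will be analyzed separately as separate cohorts for all endpoints". The synopsis states the same rule at the head of its statistical methods and lists the safety endpoints under that heading. The synopsis names the safety endpoints as "Adverse events, side effects, laboratory values", so a rule for every endpoint includes them.

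Table 8.1.2-1 has a column for cystic lesions, a column for diffuse lesions and no total. Its safety row reads "Safety endpoints | SAS | SAS". Section 8.1.1 defines the safety set as "3) Safety analysis set (SAS): Same as FAS", that is, all treated subjects. Section 8.2.3 says "For each adverse event and adverse drug reaction, the number of subjects and incidence rate are shown" and mentions neither a cohort split nor a combined summary. The target in Section 8.6.1 is "44 cases (22 cystic lesions, 22 diffuse lesions" in each stratum as listed.

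On exposure, Section 4.1.6 sets one rule for everyone: "Inject 5% ethanolamine oleate directly into the lesion at a maximum dose of 0.4 mL/kg", with a 30 mL cap per treatment. Section 4.1.8 describes one procedure. Sections 4.1.10 and 4.1.11 allow one additional treatment, at the same dosage, for diffuse lesions only. Under Section 5.2.1.1, adverse-event collection then runs to 3 months after that additional dose.

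**The concern.** Evaluating safety is one of the two stated purposes of the trial (Section 2.2). The only reason given for separation is that the two lesion types differ as diseases. The protocol does not explain why this should rule out an overall safety estimate, given that the drug, the concentration, the per-session ceiling and the injection procedure are common to both cohorts.

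Section 2.3 itself describes the drug's risks without a cystic/diffuse split: ulceration and skin necrosis in 3.0% to 14.7%, and hemoglobinuria in 41.3% to 42.9%. The natural counterpart from this trial is an overall rate, and none is planned. What is at stake is the precision of the reported rates, above all for events in the lower part of those ranges.

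**Working it through.** **The plan's own figure.** The protocol gives no precision figure for safety. The cohort size comes from the efficacy calculation for cystic lesions in Section 8.6.2 (threshold 20%, expected 50%, one-sided 2.5%, 80% power). That calculation reproduces. At n=19 the exact binomial test rejects at 8 or more responders, with type I error 0.0233 and power 0.820. At n=18 the power is 0.760. The 19 was raised to 22 for dropouts, and the diffuse cohort was set to the same number on feasibility grounds. Neither cohort was sized for safety.

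**Inputs.** n=22 per cohort and n=44 overall (Section 8.6.1). Reference rates are from Section 2.3.

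**No event of a given type observed.** The one-sided 95% upper limit is 1 − 0.05^(1/n).
- n=22: 1 − 0.05^(1/22) = 12.7%
- n=44: 1 − 0.05^(1/44) = 6.6%

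**An observed rate near the upper necrosis figure.** At 14.7% the expected counts are 22 × 0.147 = 3.2 and 44 × 0.147 = 6.5. Take 3/22 and 6/44, both 13.6%. The Clopper-Pearson 95% limits are the 2.5% quantile of Beta(x, n − x + 1) and the 97.5% quantile of Beta(x + 1, n − x).
- 3/22: 2.9% to 34.9%, width 32.0 percentage points
- 6/44: 5.2% to 27.4%, width 22.2 percentage points

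**An observed rate near the hemoglobinuria figures.** Take 9/22 and 18/44, both 40.9%.
- 9/22: 20.7% to 63.6%
- 18/44: 26.3% to 56.8%

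**Comparability of exposure.** Per session, the two cohorts follow the same rule. Over the whole trial they may not: a cystic subject has one treatment and a diffuse subject has one or two. A retreated subject can reach twice the single-session maximum and is observed for longer. An overall table must therefore identify the additional treatment.

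**The case against.** **Nothing is discarded.** A reader might infer that half of the safety data go unused. The documents do not support that. The safety set is all treated subjects, both cohorts are tabulated, and the cohorts do not overlap, so simple subject counts can be added across the two tables. This objection stands. It does not supply a planned overall result, however, and laboratory summaries such as medians cannot be recovered by combining two tables.

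**Detection is unchanged.** A reader might compare the chance of at least one case of a 3.0% event in one cohort, 1 − 0.97^22 = 48.8%, with that in both, 1 − 0.97^44 = 73.8%, and conclude that separate tables make the trial less likely to see it. They do not: 44 subjects are observed under either layout. Only the precision of the reported rates differs.

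**Exposure differs.** It is tempting to treat all 44 subjects as having the same exposure. The option to retreat diffuse lesions only, with longer follow-up, is a sound reason to keep the cohort tables. It is not a reason to omit an overall one. Section 2.3 also ties some events to lesion site, and Section 5.2.1.1 limits visual impairment to facial lesions, so neither 22 nor 44 is the right denominator for every event.

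**The statistical analysis plan could add a total.** Section 8.2.3 does not forbid one. But a plan that combined the cohorts for safety would depart from the rule in Section 8, so the protocol wording is the place to correct this.

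**Age.** Section 8.2.2.4 says "a subpopulation analysis will be conducted for four age categories" and confines it to the primary and secondary efficacy analyses. A reader might ask for the same split for safety. That is a separate preference and does not follow from this point.

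**Conclusion.** The point holds as a gap in planned reporting. The protocol applies cohort separation to safety and plans no overall safety estimate, so each adverse-event rate rests on about 22 subjects. Against an overall table of 44, the zero-event upper limit is nearly twice as high (12.7% against 6.6%), and at an observed 13.6% the exact interval is 32.0 rather than 22.2 percentage points wide.

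These figures assume that all 44 planned subjects are treated and, for the overall interval, that one event rate describes both cohorts. They illustrate the precision of the rates. Section 8.2.3 itself plans no intervals for adverse events. No stated figure in the protocol is wrong on this point. The case is for an overall summary beside the cohort tables, not in place of them.

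**What to change.** - In the synopsis and the opening of Section 8, limit the separate-cohort rule to efficacy endpoints.
- In Table 8.1.2-1 and Section 8.2.3, add an overall safety column (planned n=44) and keep both cohort columns.
- Show events from the first dose up to any additional treatment separately from events after the additional treatment. Include both periods in the overall total, counting a subject once for each type of event.

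This needs protocol wording and one extra set of tables, with no new data, visits or subjects. The small drawback is that an overall rate averages any true difference between cohorts or in exposure. The retained cohort tables still show it.

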8.1　Analysis population

8.1.1　Definition of analysis population

The population to be analyzed is defined as follows.

(1) Full analysis set (FAS): all subjects who were administered the study drug

(2) Per protocol set (PPS): The subjects in the FAS, excluding those with the following serious violations of the study protocol regulations in terms of study methods, concomitant therapy, etc. The PPS will be set for the purpose of confirming the stability of the primary analysis for the efficacy endpoints.

・Inclusion criteria violation

・Exclusion criteria violation

・Significant deviations from the study protocol that could affect the evaluation of efficacy

(3) Safety analysis set (SAS): Same as FAS

8.1.2　Endpoints and analysis populations

The analysis population for each endpoint is shown in Table 8.1.2-1. The primary analysis population for the efficacy endpoints is the FAS.

Table 8.1.2-1 Evaluation items and analysis population

| Evaluation item | Analysis population | |
| --- | --- | --- |
|  | Cystic lesion | Diffuse lesion |
| Subject basic information | FAS | FAS |
| Primary endpoint | FAS, PPS | FAS, PPS |
| Secondary endpoints | FAS, PPS | FAS, PPS |
| Safety endpoints | SAS | SAS |

8.1.3　Handling of individual cases

Prior to data fixed, the case review meeting is held, and the Coordinating Committee and the statistical analysis manager will discuss and decide on the handling of individual subjects.

8.2　Analysis policy

8.2.1　General policy

The statistical analysis manager shall prepare a statistical analysis plan prior to data fixed, and shall perform all analyses in accordance with the statistical analysis plan.

8.2.2　Efficacy analysis

8.2.2.1　Analysis for primary endpoint

For the number of subjects who achieve more than 20% reduction from baseline (prior to administration) in the volume of venous malformations at 3 months of treatment with the study drug, if the null hypothesis is "the proportion of the population achieving more than 20% reduction from baseline in the volume of venous malformations at 3 months of treatment with the study drug is less than 20%", a test based on the binomial distribution is performed. The significance level is set as 2.5% one-sided. The 95% confidence interval between the proportion of subjects achieving more than 20% reduction from baseline in the volume of venous malformations at 3 months of treatment with the study drug and the proportion based on the score test will also be estimated.

8.2.2.2　Analysis for secondary endpoints

8.2.2.2.1　Analysis for important secondary endpoints

For the symptom (pain) score associated with the target lesion at 3 months after sclerotherapy, the median -1-fold change from baseline (prior to administration) and its 95% confidence interval will be estimated. Also, a Wilcoxon signed-rank test is performed under a null hypothesis of "the median -1-fold change from baseline to 3 months after intervention in the population is less than or equal to 0." The significance level is set at 2.5% one-sided.

8.2.2.2.2　Analysis for other secondary endpoints

(1) The median percent reduction from baseline (prior to administration) and its 95% confidence interval for the reduction rate (volume) of the target lesion at 3 months after sclerotherapy will be estimated. Also, a Wilcoxon signed-rank test is performed under a null hypothesis of "The median reduction rate (volume) of the target lesion at 3 months after sclerotherapy is less than or equal to zero. The significance level is set at 2.5% one-sided.

(2) The median -1-fold change from baseline (prior to administration) to 1 month post sclerotherapy and its 95% confidence interval for the symptom (pain) score associated with the target lesion at 1 month (4 weeks) post sclerotherapy will be estimated. Also, a Wilcoxon signed-rank test is performed under a null hypothesis of "the median -1-fold change from baseline to one month after sclerotherapy in the population is less than or equal to zero." The significance level is set at 2.5% one-sided.

(3) The median change from baseline (prior to administration) to 3 months after sclerotherapy and its 95% confidence interval for the QOL score will be estimated. A Wilcoxon signed-rank test is performed under a null hypothesis of "the median change from baseline to 3 months after sclerotherapy for the population is less than or equal to zero." The significance level is set at 2.5% one-sided.

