| Main statistical methods | Due to differences in disease characteristics, cystic and diffuse lesions will be analyzed separately as separate cohorts for all endpoints.   1. Primary endpoint:   For the number of subjects who achieve more than 20% reduction from baseline (prior to administration) in the volume of venous malformations at 3 months of treatment with the study drug, if the null hypothesis is "the proportion of the population achieving mor than 20% reduction from baseline in the volume of venous malformations at 3 months of treatment with the study drug is less than 20%", a binomial distribution Tests based on the binomial distribution is performed. The significance level is set as 2.5% one-sided. The 95% confidence interval between the proportion of subjects achieving more than 20% reduction from baseline in the volume of venous malformations at 3 months of treatment with the study drug and the proportion based on the score test will also be estimated.   1. Secondary endpoints:   2.1 Important secondary endpoints  For the symptom (pain) score associated with the target lesion at 3 months after intervention, the median -1-fold change from baseline (prior to administration) and its 95% confidence interval will be estimated. Also, a Wilcoxon signed-rank test is performed under a null hypothesis of "the median -1-fold change from baseline to 3 months after intervention in the population is less than or equal to 0." The significance level is set at 2.5% one-sided.  2.2 Other secondary endpoints  1) The median percent reduction from baseline (prior to administration) and its 95% confidence interval for the reduction rate (volume) of the target lesion at 3 months after sclerotherapy will be estimated. Also, a Wilcoxon signed-rank test is performed under a null hypothesis of "The median reduction rate (volume) of the target lesion at 3 months after sclerotherapy is less than or equal to zero. The significance level is set at 2.5% one-sided.  2) The median -1-fold change from baseline (prior to administration) to 1 month post sclerotherapy and its 95% confidence interval for the symptom (pain) score associated with the target lesion at 1 month (4 weeks) post sclerotherapy will be estimated. Also, a Wilcoxon signed-rank test is performed under a null hypothesis of "the median -1-fold change from baseline to one month after sclerotherapy in the population is less than or equal to zero." The significance level is set at 2.5% one-sided.  3) The median change from baseline (prior to administration) to 3 months after sclerotherapy and its 95% confidence interval for the QOL score will be estimated. A Wilcoxon signed-rank test is performed under a null hypothesis of "the median change from baseline to 3 months after sclerotherapy for the population is less than or equal to zero." The significance level is set at 2.5% one-sided.  3. Other evaluation items  The percentage of each category (significant improvement, moderate improvement, unchanged, and exacerbation) for the change in appearance at 3 months after sclerotherapy will be estimated. We will also estimate the percentage of significant improvement or moderate improvement and its 95% confidence interval, under a null hypothesis of "the percentage of cases with significant improvement or moderate improvement is less than 20%." and then perform a test based on the binomial distribution. The significance level is set at 2.5% one-sided.  Main statistical methods  4. safety endpoints:  1) For each adverse event and adverse drug reaction, the number of subjects and incidence rate are shown. The number of subjects and the incidence rate is tabulated by organ, symptoms findings, and grade of adverse event. For serious adverse events, the number of subjects and incidence rate should be indicated and listed.  2) Summary statistics of laboratory measurements are tabulated by survey period. |

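### The secondary nulls are about the population median, but the signed-rank test prescribed for them is valid for a median only under a symmetry assumption that the protocol does not state

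*Protocol*

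**What the plan says.** Each secondary efficacy endpoint has a null hypothesis about a population median, with a signed-rank test and a median with a 95% confidence interval attached.

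- **Pain at 3 months** (8.2.2.2.1, the designated significant secondary endpoint): "the median -1-fold change from baseline to 3 months after intervention in the population is less than or equal to 0", where the change is multiplied by minus one so that improvement is positive.
- **Volume reduction rate at 3 months** (8.2.2.2.2 (1)): the estimate is "The median percent reduction from baseline (prior to administration) and its 95% confidence interval for the reduction rate (volume) of the target lesion", and the test is specified as "a Wilcoxon signed-rank test is performed under a null hypothesis of 'The median reduction rate (volume) of the target lesion at 3 months after" treatment. The synopsis repeats this null in full: "The median reduction rate (volume) of the target lesion at 3 months after sclerotherapy is less than or equal to zero".
- **Pain at 1 month** (8.2.2.2.2 (2)): built in the same way as pain at 3 months.
- **QOL at 3 months** (8.2.2.2.2 (3)): "the median change from baseline to 3 months after sclerotherapy for the population is less than or equal to zero".

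For each test, "The significance level is set at 2.5% one-sided". Cystic and diffuse lesions are analysed as separate cohorts of 22 (8.6.1), and missing values are not imputed (8.3). No symmetry assumption is stated, and the method for the median's confidence interval is not named.

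**The concern.** The signed-rank test uses the sizes of the changes as well as their signs. Its reference distribution assumes that a change of any given size is equally likely to be positive or negative. A zero median does not ensure this. It fixes the overall share of positive changes at one half but allows the positive changes to be systematically larger than the negative ones, or smaller.

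An asymmetric mix is plausible for lesion volume. Section 3.1 says these lesions generally worsen without treatment, and 8.6.2 plans for a population in which about half reach a 20% reduction. If non-responders grow slightly and responders shrink a lot, the distribution is right-skewed.

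What is at stake is the wording of the conclusion. A significant test could be reported as a median above zero when the median is zero or negative. It could also stand beside a median confidence interval that includes zero, if that interval is built from order statistics.

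**Working it through.** **The plan's own figure.** The protocol gives no error rate or power for the secondary tests. Its one computed figure is the 19 cystic cases for the primary test (8.6.2). With a 20% threshold, 50% expected and one-sided 2.5%, n = 19 with success at 8 or more responders has size 0.0233 and power 0.820; n = 18 has power 0.760. The 19 is reproduced. The secondary tests are checked at n = 22, with n = 19 as a lower evaluable number.

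**The test.** W+ is the sum of the ranks of the absolute changes over subjects whose change is positive. Its null distribution gives each rank a plus sign with probability 1/2, independently of the rank. At n = 22 the exact one-sided critical value is W+ ≥ 188 (size 0.0231).

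**Exact ceiling under median ≤ 0.** For k positive changes, W+ is largest when they hold the top k ranks: W+ = 22k − k(k − 1)/2.
- k = 11: 242 − 55 = 187, no rejection.
- k = 12: 264 − 66 = 198, rejection.

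The rejection rate therefore cannot exceed P(Bin(22, 0.5) ≥ 12) = 41.6%. At n = 19 (critical value 144), k = 9 gives 135 and k = 10 gives 145, so the ceiling is P(Bin(19, 0.5) ≥ 10) = 50.0%.

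**Simulation at n = 22 with the true median exactly 0 and no zero changes.** All shapes are assumptions; positive means reduction, in percent.

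| Assumed shape | Rejection rate |
|---|---|
| Normal, or half U(−10, 0) and half U(0, 10) (symmetric) | 2.3% |
| Gumbel (mild right skew) | 4.6% |
| Exponential, right-skewed | about 10% |
| Lognormal, two spreads | 11% and 16% |
| Half U(−10, 0), half U(0, b); b = 20, 30, 40, 60 | 14%, 23%, 29%, 34% |
| 20% N(40, 15), 80% N(0, 10), shifted to median 0 | 5.6% |
| 40% N(40, 15), 60% N(−5, 5), shifted | 23.8% |
| 50% N(40, 15), 50% N(−5, 3), shifted | 40.9% |
| Exponential, left-skewed | 0.5% to 0.6% |
| Mirror image of b = 60 | about 0.07% |

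**A negative median.** Take 45% of subjects at U(20, 60) and 55% at U(−10, 0). The median m solves 0.55(m + 10)/10 = 0.5, so m = −0.9%. The test still rejects about 24% of the time. With 30% responders, 0.70(m + 10)/10 = 0.5 gives m = −2.9%, and rejection is about 1.3% to 1.4%, below nominal.

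**Sign test.** In the median-zero scenarios where it was run it rejects 0.8% to 1.0% of the time, because it depends only on the number of positive changes.

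**Interval.** If the median's 95% CI is taken from order statistics, about 33 of the 34 percentage points of rejection at b = 60 come with an interval that includes 0.

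**The alternative null.** With skewed shapes re-centred so that the pseudomedian (median of pairwise averages) is 0, signed-rank rejection runs from about 1.4% to 6.9%.

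**The case against.** Pairing a signed-rank test with a median hypothesis is common wording. These are secondary tests, and the primary exact binomial test does not depend on them. Section 8.6.2 reads a median reduction of about 25% from a cited study, far from zero. The protocol supplies no distribution, so any inflation figure is the reviewer's. Left skew is possible too, since a reduction cannot exceed 100% while growth has no such limit, and then the test is conservative. The interval method is ordinary analysis-plan content.

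Most of this stands, and it limits the point. It does not remove it. The mismatch lies in what the protocol states, and an analysis plan that followed the text would inherit it. The 25% comes from a study that measured area, which 8.6.2 itself says is not the same evaluation. The diffuse cohort's size rests on feasibility, and no planning median exists for pain or QOL. Whether a test is valid is also judged with the null true. The primary endpoint can succeed with a negative median: in the 45%-responder mix above, it passes (9 or more of 22) about 72% of the time.

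A reader might take a figure such as 34% as this trial's error rate. It is the result of one assumed mixture, neither a maximum nor derivable from the protocol.

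**Conclusion.** The protocol's test does not control error for the protocol's null unless changes are symmetric under that null, and the protocol does not say so. The consequence is a range, not a single figure. At n = 22 with the median at 0, rejection is about 2.3% under symmetry, about 5% to 41% under the right-skewed shapes tried, and below 1% under the left-skewed ones. These rates rest on assumed shapes expressed as volume change; only the ceiling of 41.6% is free of shape.

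Three stronger readings are not supported:
- **That inflation has been shown for pain or QOL.** The wording problem applies to them, but no VAS, Face scale, EQ-5D or PedsQL change was simulated.
- **That the report will carry a p-value contradicted by its interval.** That depends on the interval method, which the protocol does not name.
- **That a pseudomedian null is exactly controlled.** It comes much closer to nominal than the median null, but is exact only under symmetry.

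Materiality is limited: the primary conclusion is untouched. What changes is what the secondary analyses, including the significant secondary endpoint, may claim.

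**What to change.** In the synopsis, 8.2.2.2.1 and 8.2.2.2.2 (1) to (3):

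1. Keep the signed-rank test at one-sided 2.5%.
2. State the null as location (pseudomedian) of the change at or below zero, and write out the assumption that changes are symmetric under it.
3. Report the Hodges-Lehmann estimate with the 95% CI obtained by inverting the signed-rank test, so that test and interval agree.
4. Keep the sample median as a descriptive statistic, and draw no conclusion about it from this test.
5. Base any claim about the median itself on a sign test with an order-statistic CI, as a supporting analysis.

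The cost is a wording change and one standard output option. No new data are needed, and the main test keeps its power. The downsides are that the pseudomedian is less familiar to clinicians and that the sign test is weaker: for an assumed normal shift of 0.7 SD at n = 22, about 55% power against 86%. That is why it is proposed only as support.
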